## **6 Study design and study procedure, sub-study 2**

### **Title: Eye-tracking of oxytocin and couple-specific behaviour**

#### ***6.1 Research question***

Sub-study 2 investigates whether oxytocin is specifically involved in the perception of couple- and/or attachment-specific stimuli in humans, compared to stimuli without a social context. Animal studies show a bonding and even "fidelity"-promoting aspect of oxytocin (Young & Wang, 2001; Insel & Young, 2001). In humans, oxytocin could be involved in close non-sexual attachment relationships (e.g. close friendships, parent-child bonds, bonds between relatives) as well as in sexual relationships, but this has not yet been investigated differentially. Animal studies also suggest a gender-specific effect of oxytocin (with stronger effects in female animals). A gender effect of oxytocin on the perception of and interest in bonding or sexual stimuli has not yet been investigated in humans.

#### ***6.2 Hypotheses***

We hypothesise that oxytocin, compared to placebo, increases interest in attachment-specific images and sexual images compared to non-social neutral control images. Furthermore, we would like to investigate a possible gender difference in relation to this effect. Since almost all studies on the effect of oxytocin have been conducted on men, we cannot yet make any assumptions about the direction of the effect in our study and formulate the hypothesis of the gender effect unspecifically.

#### ***6.3 Main target parameters***

The main target parameter in sub-study 2 is the interest in attachment-specific images or sexual images compared to non-social neutral control images. This interest is measured by the time spent looking at the images and by focusing on central image regions using eye tracking. The self-reported evaluation of the images is recorded as a secondary target parameter.

#### ***6.4 Study design***

Sub-study 2 will be conducted in accordance with ICH-GCP and in a randomized double-blind and placebo-controlled design.

#### 6.4.1 Study sample and power analyses

In sub-study 2, 88 people (44 women, 44 men) will be examined who will receive either oxytocin nasal spray or placebo nasal spray. The probability of allocation to one of the two groups is 50%. The participating women will be analysed twice during two different cycle phases. Power analyses suggest a sample size of  $N=82$  for sub-study 2 with regard to the main outcome variable preference (gaze duration) (effect  $d=.60$ ; power = .85,  $\alpha = .05$ ). With an assumed effect  $f = .50$ ,  $\alpha = .05$  and an  $N = 20$ , a power of  $\beta = .85$  can be assumed for the repeated measurement of the female participants. The total  $N$  is therefore set to  $N=88$  in order to compensate for any dropouts.

#### 6.4.2 Inclusion and exclusion criteria

The subjects must fulfil the following *inclusion criteria*:

- Women and men
- Between 25 and 45 years
- Willingness to attend one or two laboratory appointments
- Be healthy, e.g. have no acute, chronic physical, neurological, psychiatric or somatic illnesses
- Be a non-smoker (up to 5 cigarettes per day)
- fluent German
- Women: have a regular menstrual cycle (between 24 - 35 days)

*Exclusion criteria*:

- Previous participation in other studies on the topic of couple interactions or participation in another clinical study within the last 4 weeks before inclusion
- Accident with neurological sequelae
- Allergies or a history of known hypersensitivity to one of the drugs used or their ingredients, or to drugs with a similar chemical structure
- Taking medication
- Drug use, addiction or other illnesses that do not allow the person concerned to the nature, scope and possible consequences of the clinical trial
- Overweight or underweight

- Daily alcohol consumption (> 60g alcohol, equivalent to approx. 7.5 dl wine or 2 litres beer per day)
- No participation of the Investigator or his/her family members, employees or other dependent persons
- Women: hormonal contraception
- Women: Pregnancy (for instructions on the double barrier to prevent pregnancy, see subject information) or intention to become pregnant during the course of the study
- Women: Breastfeeding

These criteria are queried with the interested participants in a telephone interview. No personal details are recorded during this telephone interview, so that no personal data can be linked to the inclusion or exclusion criteria before the consent form is signed. An appointment for the study is arranged with interested and suitable participants, at which the inclusion and exclusion criteria are discussed again and the participants sign the declaration of consent.

For this study, it is essential that certain things are observed and adhered to, as these activities or factors influence the measured values and render them unusable. For this reason, the test subjects were asked to do so immediately before the study:

- Do not drink coffee or other caffeinated drinks (cola, energy drinks etc.), black tea or alcohol in the afternoon of the laboratory appointment (from approx. 3.00 pm),
- Do not engage in excessive sport on the day of the examination,
- Do not smoke immediately before the laboratory appointment,
- No physical exertion (cycling etc.) immediately before the laboratory appointment,
- Do not eat anything heavy immediately before the lab appointment.

The test subjects are recruited via circular mails from the mailing list for the recruitment of test subjects of the Psychological Institute of the University of Zurich, the description of the study in public media (ronorp, 20Minuten, NZZ), notices and websites for the recruitment of test subjects and receive CHF 50.00 per visit as compensation for participation.

### **6.4.3 Procedure of the experiment**

After a telephone interview in which inclusion and exclusion criteria are clarified, the first laboratory appointment is arranged with interested test subjects. After reading the test person information and signing the written declaration of consent at the first appointment, the test

persons receive a test person code and are given an individualised link to the study website. This link will take the test subjects to questionnaires on personality, relationship quality and chronic stress, which they can complete online. The study itself will take place in the study rooms of the Psychological Institute of the University of Zurich ([name]).

**Study information and declaration of consent:**

The potential study participants are informed about the procedure and aim of the study by means of the written information for volunteers. It is also explained to them that a pregnancy excludes participation.

**Admission procedure:**

Study participants will be asked to give their voluntary consent in writing. The enrolment examination is carried out according to the following criteria:

- Assignment of a subject number (in ascending order)
- Review of the inclusion and exclusion criteria
- Multi-drug test (urine test)
- For women: last menstruation + pregnancy test (standard urine test)

After fulfilment of the inclusion criteria, the investigator gives approval to start the study.

**Oxytocin/placebo administration:**

The subjects are then asked to take the nasal spray (24 IU = 3 sprays of 4 IU in each nostril, oxytocin or placebo in a double-blind design).

**Eye-tracking:**

45 minutes later, the test subjects will be shown a total of 90 images depicting attachment motives, explicit sexual acts or control motives in a neighbouring room after an exercise run on the computer. The test subjects can look at these pictures for as long as they like and then move on to the next picture. After each picture, they rate the attractiveness of the respective picture using a visual analogue scale (VAS). While they are looking at the images, their eye movements are recorded with an eye-tracking device using infrared. This procedure is non-

invasive, painless and completely harmless for the participants. The fixation points and fixation durations of the eye movements are recorded for each image. The length of time each image is viewed is also recorded. The images are presented using the "presentation" programme. The participants are also asked to rate each picture. After they have viewed and rated the pictures, the debriefing takes place, the subjects receive their compensation and the experiment is completed. The entire experiment takes about 2.5 hours.

## **6.5 Research methods**

### **6.5.1 Psychological examination methods**

Self-assessed health (General Health Questionnaire, GHQ-12, Banks, 1983), personal information (standardised anamnesis questionnaire on housing and living situation, socioeconomic status, etc.), personality traits (NEO-FFI, Borkenau & Ostendorf, 2008), sexual dysfunctions or experiences with - and possibly aversions to - pornographic images (German translations of the Brief Index of Sexual Function, BISF, Taylor et al, 1994, and for women the Female Sexual Function Index, FSFI, Rosen et al., 2000), as well as relationship satisfaction (German version of the Relationship Assessment Scale, RAS, Hassebrauck, 1991) are completed after signing the consent *ständniserklärung*. The assessment of the pictures is asked after each picture using a visual analogue scale.

### **6.5.2 Physiological examination methods: Oxytocin application**

Oxytocin or placebo is taken intranasally (24 IU = 3 sprays of 4 IU in each nostril) by the subjects after signing the informed consent form and completing the questionnaires in a double-blind design.

### **Compliance**

The compliance of the test subjects with regard to taking their medication can be observed directly in sub-study 2.

### **Pre-treatment and concomitant therapy**

No other treatments or medications are permitted during the study. Any concomitant therapies will be requested at the start of the study. All possible concomitant and/or emergency medication(s) must be documented in the CRF.

## **Packaging, labelling and delivery**

The test preparation is given to the test subjects in the form of clearly labelled nasal sprays. The labels on the nasal sprays provide instructions on the dosage in which the nasal spray should be taken (see labels in the appendix). The study medication will be provided by KAZ. The nasal sprays will be collected in tranches of 10 sprays each by the study coordinator and stored in a lockable refrigerator in a restricted-access room at the Institute of Psychology until the experiment. Upon receipt of the study medication/study material, an inventory is taken, a Drug Receipt Log is filled out and signed by the person who received the material. A thorough check is made to ensure that the consignment contains all the items on the delivery note. If the delivery contains defective or unusable study medication, this is recorded in the study documents. Regular drug reconciliation regarding allocation, administration and remaining study medication will be performed, documented with the Drug Reconciliation Form, and dated and signed by the study team. At the end of their participation in the study, the nasal sprays will be collected and documented by the study management. The returned nasal sprays will be kept until data collection is completed to enable any cross-checks with regard to blinding.

## **Blinding**

The study is a placebo-controlled double-blind study. This means that the placebo contains all the same ingredients as the original medication - except for the active ingredient. The preparation of the placebo and blinding of the study medication is carried out by KAZ. The preparation of the placebo and blinding of the study medication is carried out by KAZ (GMP certificate see appendix). An assistant from the Chair of Clinical Psychology and Psychotherapy (lic. phil. [name]) who is not involved in the study will carry out the randomisation using the "Research Randomizer" program and submit the randomisation table to KAZ. The KAZ will hand over the table sealed in an envelope to the study management after the preparation of the test sample. This allows the investigator to unblind the code in an emergency. The code should only be broken in an emergency if the identity of the preparation must be known to the investigator in order to ensure the medical care of the participating person. After completion of data collection, the blinding is cancelled.

## **Storage conditions**

The study medication is stored refrigerated in the KAZ. The unopened medication has a shelf life of three years. As the medication is not opened for blinding, all medication can be ordered and stored in one batch.

### **Return or destruction of the study medication**

At the end of the study, a final review of the transport, dispensing and whereabouts of the study medication is carried out. This is documented with the Drug Reconciliation Form, dated and signed. Any discrepancies will be investigated, clarified and documented before any remaining study medication is destroyed. The destruction of the study medication is then recorded in the study documents.

## ***6.6 Collected data and data analyses***

### **6.6.1 Behavioural and self-report data**

In addition to the persistent and self-reported masses, eye-tracking data is collected as behavioural data, as described above. The data is analysed using the program supplied with the eye tracker ("Tobii Studio™ Analysis Software"). For this purpose, different areas of interest (AOI) of the images are compared with each other in terms of gaze duration and frequency. The self-report and eye-tracking data are analysed at the Department of Clinical Psychology and Psychotherapy of the Institute of Psychology at the University of Zurich (Head: [name]. [name]). The evaluation of this data is carried out in strict compliance with the anonymisation of the test subjects (see below).

## **7 Risk-benefits ratio and ethical considerations**

Couple relationships and marriages are clearly associated with health and longevity and significantly better survival rates after health threats such as cancer and myocardial infarction. The psychobiological mechanisms underlying this protective effect of close relationships are not yet known. However, a buffering effect of closeness and social support during stress is suspected. A recently published study investigating the effect of social support and couple conflict behaviour on wound healing was also able to show that couple conflict and, in particular, hostile interaction during couple interactions delayed wound healing. It remains to be found out which neuronal mechanisms cause this effect in the central nervous system.

Previous studies have shown that the nonapeptide hormone oxytocin is particularly involved in the regulation of bonding behaviour and pair interaction at the central nervous level and attenuates the neuroendocrine stress response. Data from non-human mammals suggest that oxytocin-induced suppression of the HPA axis supports wound healing. This effect has not yet been studied in humans, but it is hypothesised that the same interaction mechanisms of stress, oxytocin and wound healing are present as in non-human mammals.

Wound healing in the context of stress vs. social support has very important clinical implications, for example for recovery after surgery, but also for wounds in everyday life. Therefore, the identification of mechanisms that may influence the relationship between stress, social interaction and wound healing on a neuronal level is highly relevant for behavioural medicine disorders and health in general.

### ***7.1 Ethical aspects***

The project and its sub-studies will be conducted in accordance with the ethical guidelines of the Helsinki Declaration and comply with the ICH-GCP standard. A drug will be used that is authorised on the Swiss market and for which no serious side effects have been reported in previous studies. The following measures will be taken to ensure subject safety, confidentiality and data integrity:

### ***7.2 Confidentiality of respondent data***

All subjects are assigned an identification number (in ascending order) when they first register. All materials collected will be labelled with this number. Only the consent form will contain both the name and the number and will be stored separately from all data in a sealed box.

No data will be analysed by name, only by subject number, and there will be no way to link the name to the ID number other than through the consent form. All psychological and biochemical data will only be identifiable by code number. No publication of this project will disclose the names of the subjects.

### ***7.3 Potential risks and protection against risks***

The risks to subjects in this project and the sub-studies are low. Nevertheless, there are areas of potential risk associated with intranasal oxytocin administration and bladder wound induction.

#### **7.3.1 Syntocinon (oxytocin) nasal spray**

Syntocinon-Spray® is a well-tolerated medicine that is widely used in obstetrics. The nasal spray may cause slight irritation of the nasal mucosa with increased secretion. In rare cases, allergic reactions, nausea, vomiting or headaches have been reported, as well as abdominal pain due to uterine contractions. Occasionally, oxytocin causes an increase in blood pressure, rarely a drop in blood pressure, which may be accompanied by reddening of the skin and reflex tachycardia. However, studies on healthy volunteers have so far shown no side effects following the administration of oxytocin nasal spray. We do not expect any side effects when using the nasal spray. We ask the test subjects to report any symptoms to us immediately so that they can be treated.

#### **7.3.2 Suction blister application, measurement of wound fluid and measurement of the wound**

The application of the suction blisters to the arm results in a small wound. This wound may cause slight pain. Removing the wound fluid can also be painful. In very rare cases, the wound may become inflamed, be painful for longer and leave scars. No medical side effects are to be expected when the wound is measured after one week.

We will apply the suction blisters and measure the wound fluid in accordance with international standards and under sterile conditions. In addition, the test subjects are asked to report any symptoms or pain to us immediately so that they can be treated.

### 7.3.3 For women of childbearing age

As Syntocinon spray can lead to uterine contractions towards the end of a pregnancy and can trigger milk production, it must not be used in pregnancy except for these medical implications. We therefore carry out a standard pregnancy test on all female participants before the start of the study. In the study, a double-barrier method of contraception is used to prevent pregnancy, i.e. the study participants use two reliable methods of contraception during the study (in sub-study 1: pill in combination with -, otherwise double mechanical contraception, e.g. diaphragm, IUD etc. in combination with condoms). Patients who become pregnant during the study must inform their doctor immediately and may not continue to participate in the study. In this case, they are asked to consult a specialist doctor so that specialist medical care is ensured and to provide information on the course and outcome of the pregnancy (see also 7.5.1). Women who are breastfeeding are excluded from participation in the study. In order to rule out the possibility of pregnancy occurring during the study in everyday life, we examine all our participants during the luteal phase (day 16 - 28 of the menstrual cycle).

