#### 5.4.2 Inclusion and exclusion criteria

The subjects must fulfil the following *inclusion criteria*:

- Heterosexual couple
- Between 25 and 45 years old
- In a stable relationship for at least one year (maximum 15 years) and living together
- No children
- Willingness to attend three laboratory appointments and carry out independent measurements at home
- Be healthy, e.g. have no acute, chronic physical, neurological, psychiatric or somatic illnesses
- Be a non-smoker (up to 5 cigarettes per day)
- fluent German
- Women: have a regular menstrual cycle (between 24 - 35 days)

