#### *Exclusion criteria*

- Indications that the participant is unlikely to comply with the test plan (e.g. unwillingness to cooperate)
- Participation in another clinical trial within the last 4 weeks prior to inclusion
- Skin disease
- Accident with neurological sequelae
- Allergies or a history of known hypersensitivity to one of the drugs used or their ingredients, or to drugs with a similar chemical structure
- UV-B irradiation in the last 3 months before the examination
- Taking medication
- Drug use, addiction or other illnesses that do not allow the person concerned to the nature, scope and possible consequences of the clinical trial
- Overweight or underweight
- Daily alcohol consumption ( $> 60g$  alcohol, equivalent to approx. 7.5 dl wine or 2 litres beer per day)
- No participation of the Investigator or his/her family members, employees or other dependent persons
- Women: Pregnancy (for instructions on the double barrier to prevent pregnancy, see subject information) or intention to become pregnant during the course of the study

- Women: Breastfeeding

These criteria are queried with the interested participants in a telephone interview. No personal details are recorded during this telephone interview, so that no personal data can be linked to the inclusion or exclusion criteria before the consent form is signed. An appointment for the study is arranged with interested and suitable test subjects, at which the inclusion and exclusion criteria are discussed again and the test subjects sign the declaration of consent.

For this study, it is essential that certain things are controlled, as these activities or factors influence the measured values and may make them unusable. For this reason, the test subjects were asked to follow the instructions bellow:

- Do not drink coffee or other caffeinated drinks (cola, energy drinks, etc.), black tea or alcohol on the afternoon of the first laboratory appointment (approx. from 3 pm),
- Do not engage in excessive sport on the day of the examination,
- Do not smoke immediately before the 1st laboratory appointment,
- No physical exertion (cycling etc.) immediately before the 1st laboratory appointment,
- Do not eat anything heavy immediately before the 1st lab appointment.

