### Admission procedure:

Study participants are asked to give their voluntary consent in writing. The investigator may only begin the study-specific examinations once the declaration of consent has been received. The enrolment examination is carried out according to the following criteria:

- Assignment of a subject number (in ascending order)
- Review of the inclusion and exclusion criteria
- Multi-drug test (urine test)
- For women: last menstruation + pregnancy test (standard urine test)

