## **5.6 Physiological examination methods**

### **5.6.1 Intranasal application of oxytocin**

In a double-blind and placebo-controlled design, participants will take oxytocin (Syntocinon, Novartis, Basel, Switzerland) or placebo intranasally at the first laboratory appointment and then twice daily for 5 days after the first laboratory appointment:

During the 1st laboratory appointment, the subjects take 24 IU (3 sprays in each nostril) before the instruction of the standardized positive interaction/no interaction.

On the day of the first laboratory appointment, the test subjects are asked to spray 2 bursts of oxytocin or placebo into each nostril at 2 times on the following 5 days (together with the saliva vial measurements 4 & 5) (a total of  $2 \times 2 \times 4 \text{ IU} \times 2/\text{day} = 32 \text{ IU}$ ). This procedure is maintained on the following 5 measurement days at home. In total, the test subjects will therefore

ingest 1\*24 and 5 \* 32IU of either oxytocin or placebo (Ditzen, Schaer et al., 2009; [name] et al., 2003; Kosfeld et al., 2005).

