### **5.7.2 Biological data**

The hormonal data (salivary cortisol) and the salivary enzyme alpha amylase will be analyzed in the psychobiological laboratory of the Department of Clinical Psychology and Psychotherapy of the Psychological Institute of the University of Zurich (Head: [name]. [name]).

The following parameters will analyzed as wound healing parameters:

- Size of the wound (photographed with measuring tape immediately after wound application and 7 days after wound application)
- Trans-epidermal Water Loss (TEWL; using an evaporimeter before wound application, immediately after removal of the epidermis, 24 hours after removal of the epidermis, 7 days after removal of the epidermis)
- Epithelialisation (by microscopy before wound application, immediately after removal of the epidermis, 24 hours after removal of the epidermis, 7 days after removal of the epidermis)
- Mediators of wound healing: cytokines in the wound fluid (TNF alpha, IL1, IL6; analysis of the wound fluid 1) from two blisters immediately after application of the suction blisters, 2) from two intact blisters 24 hours after application of the suction blisters).

The evaluation of the data on wound size, TEWL and epithelialization will be carried out in the Dermatology Department of the USZ. The cytokine concentrations are analyzed by the Cytolab laboratory ([name], [name]). All data will be analyzed in strict compliance with the anonymization of the subjects (see below).

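### In sub-study 1 the fixed day 16–28 window is not the luteal phase in longer admitted cycles, so for women not on the pill it does not work as the added pregnancy safeguard that the protocol states

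*Protocol*

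**What the plan says.** Protocol section 7.3.3 ends with a timing rule for women. Its purpose is introduced by "In order to rule out the possibility of pregnancy occurring during the study in everyday life", and the rule itself is "we examine all our participants during the luteal phase (day 16 - 28 of the menstrual cycle". The same section states that "the study participants use two reliable methods of contraception during the study". In sub-study 1 the pill may be one of them; otherwise mechanical methods are used.

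The sub-study 1 inclusion criteria in section 5.4.2 read "Women: have a regular menstrual cycle (between 24 - 35 days". The spray is taken at the first appointment and then, under section 5.6.1, "twice daily for 5 days after the first laboratory appointment". The entry check in section 5.4.4 is "For women: last menstruation + pregnancy test (standard urine test"; no ovulation test is listed. Wound size is recorded "immediately after wound application and 7 days after wound application" (section 5.7.2).

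The timing rule can only concern sub-study 1. Sub-study 2 has no home dosing, and section 6.6.2 compares the follicular with the luteal phase in women.

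**The concern.** A fixed range of cycle days cannot be the luteal phase for every cycle length between 24 and 35 days. In longer cycles ovulation falls inside the range, so the window can place ovulation within the dosing week instead of behind it. Women using mechanical contraception still ovulate.

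The entry test cannot show a conception that occurs later, during the home week. The window is offered to close exactly that gap. What is at stake is the truth of a safety statement in the risk section and the working of one added safeguard. Power and the treatment comparison are not touched.

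**Working it through.** **Inputs.** Window: days 16 to 28 (section 7.3.3). Cycle length L: 24 to 35 days, 12 values (section 5.4.2). Home dosing: the 5 days after the first appointment (section 5.6.1). Last measurement: 7 days after wound application (section 5.7.2). Luteal length is not in the protocol and is an assumption here: 14 days, range 12 to 16.

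**Formulas.** Ovulation day = L − luteal length. Luteal phase = the day after ovulation up to day L. With the first appointment on day s, home doses fall on days s+1 to s+5.

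**The protocol's own window.** Days 16 to 28 are exactly the luteal phase only if L = 28 and the luteal length is 13, since 28 − 13 + 1 = 16. In a 35-day cycle with a 14-day luteal phase ovulation is on day 35 − 14 = 21, so days 16 to 21, 6 of the 13 window days, are not luteal (4 of 13 with 16 days, 8 of 13 with 12 days).

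**Permitted starts.** If the 7-day measurement must also fall by day 28, then s + 7 ≤ 28 and s runs from 16 to 21. That is 6 starts, and 6 × 12 = 72 combinations.

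**Count.** A combination counts if s+1 ≤ L − luteal length ≤ s+5, that is, if ovulation falls on a home dosing day. The cells give the number of cycle lengths that qualify:

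| Luteal length | s=16 | 17 | 18 | 19 | 20 | 21 | Total of 72 | Shortest cycle affected |
|---|---|---|---|---|---|---|---|---|
| 12 | 5 | 5 | 5 | 4 | 3 | 2 | 24 | 29 |
| 13 (implied by the window) | 5 | 5 | 4 | 3 | 2 | 1 | 20 | 30 |
| 14 | 5 | 4 | 3 | 2 | 1 | 0 | 15 | 31 |
| 16 | 3 | 2 | 1 | 0 | 0 | 0 | 6 | 33 |

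Example: with 14 days and s = 16, home doses fall on days 17 to 21. Ovulation falls on days 17, 18, 19, 20 and 21 for L = 31 to 35, which gives 5 lengths. The shortest affected cycle is 17 + luteal length.

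**Other reading of the last visit.** The visit plan shows the last visit as day 6. Then s + 5 ≤ 28, s runs from 16 to 23, and there are 8 × 12 = 96 combinations. Ovulation is at most day 21 with a 14-day luteal phase, so s = 22 and 23 add nothing: 15 of 96. With 12 days, s = 22 adds one (L = 35, ovulation on day 23): 25 of 96. With 16 days it is 6 of 96.

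**Short cycles.** At the other end the window outlasts the cycle. With s = 20 and L = 24, or s = 21 and L = 24 or 25, some home doses fall after day L, in the next cycle. They are not luteal either, but they are not included in the counts above.

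**The case against.** The best case for the protocol has four parts.

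- **The governing words are right.** The sentence requires the luteal phase, and the days in brackets may be only a gloss for a 28-day cycle. This has some force, but the days are the only operational rule given, they are applied to all participants, and no ovulation check is listed that would override them.
- **The window is redundant.** Women use two contraceptive methods, section 7.3.4 asks the same of men, a pregnancy test is done at entry, and women intending pregnancy are excluded. This stands and keeps the point minor. It does not make the statement correct.
- **The risks that section 7.3.3 names are remote.** They are contractions late in pregnancy and milk production, not effects on a conception a few days old. This also stands and bears on severity.
- **The counts weight start days and cycle lengths equally**, and their denominator depends on how the visit rule is read: 6 or 8 starts, or 13 if only the first appointment must lie in the window. This is true, and the counts show only that the failure lies inside the permitted range.

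A reader might go further and infer that women are unprotected against pregnancy, or that cycle phase biases the oxytocin comparison. The documents support neither. The other safeguards remain, and section 5.7.3 compares oxytocin with placebo and men with women, with no cycle-phase factor.

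A reader might also take the number of home doses given before ovulation as the measure of failure. That is the wrong quantity. In a 35-day cycle with a 12-day luteal phase and a day 16 start, all five home doses precede ovulation on day 23, so none follows it. In a 31-day cycle with a 14-day luteal phase ovulation falls on day 17, the first home dosing day, and four more dosing days follow. The second case is the one that the safeguard is meant to prevent.

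**Conclusion.** The point holds as a minor error in a stated safety rule for sub-study 1. For women not on the pill, cycles from 31 days (range: from 29 to from 33) allow ovulation on a home dosing day after an early permitted start. With a 14-day luteal phase the latest such start is day 20. The size, 15 of 72 combinations (range 6 to 24), rests on the assumed luteal length, on ovulation at L minus that length, and on the last measurement falling by day 28.

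How many women this concerns cannot be derived, because the protocol gives neither the distribution of cycle lengths nor the share on the pill. The direction does not depend on the assumption: longer admitted cycles are affected at every luteal length from 12 to 16 days.

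**What to change.** In section 7.3.3, for women not on the pill, replace the fixed days by: the first appointment lies between day L-11 and day L-7 of the woman's usual cycle length L. This gives days 17 to 21 for L = 28, 21 to 25 for L = 32 and 24 to 28 for L = 35. The eight days from wound application to the 7-day measurement then run from day L-11 at the earliest to day L at the latest. With luteal lengths of 12 to 16 days ovulation is on day L-12 or earlier, so none of the 5 × 12 = 60 combinations has a study day on or before ovulation or after day L. The rule has a limit: with a 10-day luteal phase ovulation is on day L-10, the first home day after a day L-11 start. If only the dosing days need to be luteal, the window can run to day L-5.

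Limit the sentence to sub-study 1, and say that the timing further reduces the chance of pregnancy instead of excluding it.

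The cost is small. There are 5 possible start days per cycle (7 if the window runs to L-5), against 6 now if the last visit is the 7-day measurement, or 8 if it is day 6 as in the visit plan. Usual cycle length must be asked at booking along with last menstruation. Section 5.4.2 says "No personal details are recorded during this telephone interview", which can still be met if only the appointment date is kept. No extra visits or participants are needed.
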